### **4.3.4. Reducing physical activity (V)**

The analysis was conducted using the “intention-to-treat” (ITT) approach, including all randomized subjects which took at least one dose of the study preparation/or intervention and who had at least one post-baseline efficacy variable measurement. Changes between baseline and after intervention period was analyzed with paired t-tests. The absence of studies evaluating the immunological outcomes precluded the power analysis.

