### **Methods:**

Study design: An observational study with validation methodology will be applied to evaluate respiratory infections; in prospective cohort study of 12 weeks a group of athletes under high competition levels, respiratory infections and potential risk factors accordingly to literature will be evaluated; an prospective case-control with a moderate- exercise program intervention will compare the impact in respiratory infections in elderly under exercise training or not; a randomized, placebo controlled cross-over trial will evaluate the impact of a high fat/high energy meal challenge in an acute exercise challenge; randomized clinical trial will be used to ascertain the impact of physical activity reduction in the immune function

Selection of participants: For questionnaire validation will be selected participants with respiratory infections; athletes will be selected from a high elite pre-competition level team; elderly will be selected from general population, namely from senior universities and nursing homes; asthma and obese participants will be selected from an university population sample

Sample Size: 281 patients will be chosen as target for evaluation in respiratory tract infections validation; 40 patients will be evaluated in total in swimmers illness-prone study trial; 40 participants will be selected to evaluate exercise program in the elderly; 30 participants, with a

equal number of obese, asthma, obese and asthma and a control will be allocated to the meal interventions (60 participants in total) and a target of 60 participants will be randomized to the physical inactivity intervention.

Measurements: Upper respiratory tract infections number, severity and quality of life impact, immune system markers, complete blood cell count, pro-inflammatory and anti-inflammatory mediators, namely cytokines, and metabolomic.

Main Outcomes: Respiratory Infection Risk in Susceptible Population, Immune markers parameter related with acute exercise and physical inactivity interventions (balance between pro-inflammatory and anti-inflammatory cytokines).

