#### **4.1.5. Physical activity reduction effect on immune response (V)**

This is a randomized controlled trial where participants, after a run-in period and eligibility evaluation, will be randomized to an intervention consisting in a reduction of physical activity by 50% or maintaining habitual physical activity for two weeks. Participants will be recruited from the same population as the meal-exercise challenge study and stratification will be done accordingly to having asthma and  $BMI \geq 30 \text{ kg/m}^2$  in order for both characteristics could be balanced between groups.

Participants will be at baseline characterized for their nutritional status, dietary habits and physical activity through questionnaire and basal assessment of all sports activity practiced during a week. Also generic quality of life questionnaire will be applied. A pedometer and accelerometer will be used to monitor physical activity. After this run-in period, if they have an adequate physical activity they will be allocated randomly to one of the interventions. Calculation of physical activity reduction will be performed individually, and a daily steps target will be demanded for each group. Both groups will use a pedometer during 3 weeks, except during the night or at circumstances that the device might be damaged (bath). They will be able to monitor if they achieved or exceeded the target number of steps for that day. Keeping the same regular diet without any new changes will be requested and new recall dietary assessment will be also performed in the end of the study. Immune function mediators will be the primary outcome to be assessed before and after the intervention period in both groups. As secondary outcomes endocrine and metabolomic evaluation will be performed.

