#### Randomization

Stratified blocked randomization will be performed accordingly to being asthmatic or obese. This methodology was chosen in order for both groups to be balanced for intervention comparison. Neither the participants or investigator team will be blind to the intervention procedure as there is a need to monitor number of steps/day to be compliant with the prescribed physical activity diary (keeping the same mean steps or reducing by 50% the number of steps/day). Equal number of participants will be allocated to each group.

Allocation concealment will be prevailed as investigator and participant will only know the intervention that they will be submitted at the second visit.

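### Study V randomises two arms, but its analysis section names only paired baseline-to-end t-tests and no between-arm test of the primary outcome

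*Protocol*

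**What the plan says.** Section 4.1.5 describes Study V as a parallel-group trial in which participants are "randomized to an intervention consisting in a reduction of physical activity by 50% or maintaining habitual physical activity for two weeks". On the outcome it says: "Immune function mediators will be the primary outcome to be assessed before and after the intervention period in both groups".

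The Randomization paragraph of 4.1.5 gives the allocation method: "Stratified blocked randomization will be performed accordingly to being asthmatic or obese". It states the purpose, "This methodology was chosen in order for both groups to be balanced for intervention comparison", and the ratio, "Equal number of participants will be allocated to each group". The Summary gives the size: "a target of 60 participants will be randomized to the physical inactivity intervention".

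The analysis section for this study, 4.3.4, defines an intention-to-treat set and then names one method: "Changes between baseline and after intervention period was analyzed with paired t-tests". It mentions no difference between arms, no baseline-adjusted model and no group-by-time term.

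Section 4.3, which is headed as covering Studies I to V, lists Student's t-test for normally distributed continuous data, Mann-Whitney for group comparisons of non-normal data, and log transformation for skewed data. It does not say which of these applies to Study V, to change scores or to the primary outcome.

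**The concern.** The method named does not match the design. In Study IV each participant eats both meals, so a paired test there compares the two interventions. In Study V each participant receives one allocation only, so a paired test compares the person with himself or herself two weeks earlier. Whether it is run within each arm or on all participants pooled, the result contains no estimate of the randomised contrast.

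Anything that shifts markers in both arms over the period then counts towards significance. Wearing a pedometer and working to a daily step target, which section 4.1.5 asks of both groups, could have such an effect, as could season or repeat sampling. If the report shows one p-value per arm, a reader may take significance in one arm and not in the other as evidence of an effect, which it is not. The trial could then claim an effect on immune markers without having used its control arm for the purpose that the Randomization paragraph gives.

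**Working it through.** The protocol states no power, effect size or SD for Study V, so there is no figure of its own to reproduce. The check asks how a within-arm paired test behaves when the intervention does nothing.

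**Inputs**
- Participants: 60 (Summary), allocated equally (4.1.5, Randomization), so 60 / 2 = 30 per arm. No dropout is deducted, because none is stated.
- Significance level: 0.05 (4.3). Two-sided is my assumption.
- Shared shift d, in units of the SD of the individual change, the same in both arms. The protocol gives none, so a range is shown.

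**Within-arm paired t-test.** With n = 30 the statistic is noncentral t with 29 degrees of freedom and noncentrality d × √30. Let p be the probability of two-sided significance in one arm. The arms are independent, so:
- exactly one arm is significant with probability 2p(1 − p);
- only the step-reduction arm is significant with probability p(1 − p).

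| Shared shift d (SD of change) | p, step-reduction arm | Exactly one arm | Step-reduction arm only |
|---|---|---|---|
| 0 | 0.050 | 0.095 | 0.048 |
| 0.1 | 0.083 | 0.152 | 0.076 |
| 0.2 | 0.185 | 0.302 | 0.151 |
| 0.3 | 0.355 | 0.458 | 0.229 |
| 0.37 | 0.500 | 0.500 | 0.250 |
| 0.5 | 0.754 | 0.371 | 0.186 |
| 0.7 | 0.959 | 0.078 | 0.039 |

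Example at d = 0.3: 2 × 0.355 × 0.645 = 0.458. The product 2p(1 − p) cannot exceed 0.5 and reaches it at p = 0.5, so the row at 0.37 SD is the worst case for discordance.

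**Between-arm test.** The shared shift cancels in the difference between arms, so the false-positive rate is 5% in every row.

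**Precision of a between-arm comparison of change, 30 per arm.** By the normal approximation, the difference detectable at 80% power is (1.960 + 0.842) × √(2/30) = 2.802 × 0.258 = 0.72 SD of change. The exact t calculation gives 0.74 SD. By the normal approximation, power is 49% at 0.5 SD, 77% at 0.7 SD and 87% at 0.8 SD.

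**The case against.** The strongest reply is that the arms will in fact be compared. Section 4.3 covers all five studies and includes two-sample tests, 4.3.4 is a subsection that can be read as adding to it, and the Randomization paragraph says a comparison is intended. This stands as far as it goes. A reader might infer that the arms are never compared, or that 4.3.4 overrides 4.3. The documents say neither. They do leave the between-arm test unassigned while assigning a paired test to the baseline-to-end changes, which are what the primary outcome measures.

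A second reply is that a statistical analysis plan may supply the test. If the protocol were silent, that would be enough. Here it positively names a method that does not answer the randomised question, so the two documents would conflict.

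A third reply is that the error rates rest on assumed shifts, and that no passage says significance in one arm only will be read as an effect. Both statements are correct. The 50% figure is a maximum, and with no shift discordance is about 10%. The discordance figures show what follows if results are read that way.

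One might also fault the statement "The absence of studies evaluating the immunological outcomes precluded the power analysis" by pointing to the IL-6 standard deviations of 1.3 and 0.5 used for Study IV. I would not. Section 4.3.3 takes them from acute meal or exercise challenges and itself says the first cannot be generalised to its population. They are a poor basis for a two-week change in habitual activity.

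**Conclusion.** The point holds in this form: 4.3.4 specifies only paired tests for a randomised two-arm trial and ties no between-arm test to the primary outcome. It needs correction, because this is the only study-specific analysis given for Study V and it neither estimates nor tests the effect of the intervention.

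Under no arm effect, the chance that the step-reduction arm looks significant rises from 5% without a shared shift to 75% at a shared shift of 0.5 SD of change. The mismatch between test and design needs no assumption. The percentages assume 30 completers per arm, roughly normal changes, a two-sided level of 0.05 and the shift sizes shown.

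**What to change.** Replace the paired-test sentence in 4.3.4 with wording such as: *The primary analysis of each primary immune marker is the difference between randomised arms at the end of the intervention, with its 95% confidence interval, from an analysis of covariance with randomised arm, the baseline value of the marker, asthma and obesity as terms. Markers with skewed distributions are analysed on the log scale. Within-arm paired tests are descriptive only.*

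A two-sample comparison of change would also test the right contrast. ANCOVA is preferable because it uses the baseline value and the stratification factors. The log scale is already allowed by 4.3.

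Optionally, add the precision of the fixed sample in SD units: with 30 per arm, about 0.74 SD of change is detectable at 80% power by a two-sample comparison, and less with baseline adjustment. This needs no borrowed standard deviation. Whether to name a single primary marker is a separate decision and not part of this change.

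The cost is protocol wording. Markers before and after, asthma history, weight and height are all already to be collected, and the sample size and visits stay as they are.

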## 5. Safety

An Adverse Event (AE) is any untoward medical occurrence in a patient regardless of its causal relationship to the study treatment. An AE can therefore be any unfavorable and unintended sign, symptom or disease, temporally associated with the trial. The occurrence of an AE may come to the attention of study personnel during the study interviews or procedures or upon review by a study monitor. All AEs including local and systemic reactions not meeting the criteria for “serious adverse events” will be registered (event description, time of onset, clinician’s assessment of severity), relationship to study procedures will be searched. All AEs will be followed to adequate resolution. Any medical condition that is present at the time that the subject is screened will be considered as baseline and not reported as an AE. However, if it deteriorates at any time during the study, it will be recorded as an AE. All AEs will be assessed by the clinician using a protocol defined grading system: mild, events require minimal or no treatment and do not interfere with the subject’s daily activities; moderate, events result in a low level of inconvenience or concern with the therapeutic measures and severe, events interrupt a subject’s usual daily activity and may require systemic drug therapy or other treatment. As relationship to the study is concerned an AE will be classified in: associated, event is temporally related to the administration of the study product and no other etiology explains the event and not associated, event is temporally independent of study product and/or the event appears to be explained by another etiology.

A serious adverse event is defined as an AE that meets one of the following conditions: death during the period of protocol-defined surveillance; life-threatening event (defined as a subject at immediate risk of death at the time of the event); inpatient hospitalization or prolongation of existing hospitalization during the period of protocol defined surveillance and any other important medical event that may not result in death, be life threatening, or require hospitalization, but based upon appropriate medical judgment, the event may jeopardize the subject and may require medical or surgical intervention to prevent one of the outcomes listed above.

### Safety

No safety issues will come from the participation in the respiratory symptoms survey study (I), as only observational data will be retrieved. Data confidentiality will be preserved and the questionnaires will be identified by a number.

For the illness-prone evaluation profile (II), baseline assessment procedure as well as measures were previously submitted and accepted by the ethical commission (**Attachment-5**).

For lung function evaluation and testing procedures the following risk and safety measures will be considered:

- Lung function will be assessed by spirometry and bronchodilation response will be evaluated by salbutamol, all good practice guidelines will be followed[54]. These are

safe procedures only a possible discomfort related with forced expiratory maneuvers can be felt, but no adverse reactions are expected.

- In capsaicin challenge in a recent review adverse events were investigated and only minor side effects like throat irritation, self-solved feeling was reported during the procedure [71]. Published contra-indications will be respected[55].
- Methacoline challenge is a standardized procedure widely use for bronchial hyper-responsiveness assessment[60], accordingly to guidelines, a medical trained doctor trained in evaluating and treating bronchospasm will be present at all times and appropriate resuscitation equipment available. Contra-indications published in the guidelines will be respected[60].The procedure will be performed in total safety conditions starting from very small doses and in stepwise, as soon as positive criteria is achieve or any symptom occurs procedure is stopped and will be given inhaled salbutamol to reverse bronchial constriction. Transient symptoms can occur namely dyspnea, cough and chest tightness but will be immediately treated. Participant will be discharged when he returns to their baseline spirometry values and his symptomless.
- Exhaled nitric oxide, exhaled breath condensate measurements were not associated in the literature to safety problems, risks or complications[72].
- Induced sputum is a safe procedure, pre-treatment with salbutamol is used to avoid potential side effects and lung function will be monitored during the procedure with peak expiratory flow, when symptoms occur or a drop occurs in lung function the participant is immediately treated and broncho-constriction reversed. There are no reports of death or need for hospital admission in patients undergoing sputum induction[73].

Pupillometry (II, IV) is a non-invasive method, through an extensive search through databases for “safety”, “risks”, “complications”, and “safety” associated with “pupillometry” retrieved no results concerning potentials risks for this procedure were found. Contraindications, which will be strictly followed, include avoidance when the orbit structure is damaged or surrounding soft tissue has an open lesion or edema.

Blood sampling (II, III, IV and V) will be performed accordingly to the published recommendations and hygiene measures will be followed[74]. Risks related to phlebotomy have been previously described namely infection risk, light-headiness and local hematoma. All potential adverse effects will be registered and oriented by the researcher team. No adverse effects, except the inconvenience will be related with urine and saliva samples collection. The prick-puncture test is safe[57]. Systemic reactions with skin prick tests for inhalant extracts are rare and have decreased dramatically to an overall risk below 0.02% for anaphylactic reactions and no fatalities with aeroallergen commercial extracts have been reported[57]. Mild reactions are expected to occur in 15 minutes (defining a positive test) in a skin prick test local wheal, itching, and erythema. Delayed or systemic reactions are unexpected.

Exercise testing (IV), namely maximal symptom-limited exercise testing is a relatively safe procedure, especially in otherwise healthy individuals. Fatality risk is related to medical complications to the underlying disease and the rate of death per patients during exercise testing is 2 to 5 per 100.000[75]. Strict contra-indications will be followed. A licensed physician and an cardio-respiratory technician will observe the participant during exercise and the recovery period and watch for undue stress (e.g., severe wheezing, chest pain, lack of coordination) or adverse signs (e.g., ECG abnormalities, falling blood pressure, decrease in O2 saturation), if it occurs the test will be immediately stopped and any adverse event treated. A resuscitation cart will be immediately available. The population tested in this study will be young and otherwise healthy without know disease, only chronic co-morbidity will be asthma and obesity. Exercise induced bronchoconstriction is assessed by exercise challenge and it is a recommended and widely used method to evaluate asthma patients. Furthermore these population will be under controlled asthma. If any adverse event occurs, namely bronchoconstriction it will be immediately reversed with bronchodilation.

Exercise intervention in the elderly population (III), was already submitted and accepted by the ethical commission (**Attachment 6**). Moderate exercise program will be performed and adapted to each elderly participant, co-morbidities and difficulties and physical condition and anaerobic resistance for exercise strength will be evaluated previously to the training by resistance maximum. Exercise will then be adapted to each individual condition and progressively increased at each participant rhythm. The exercise will be guided by sports professors trained in exercise teaching and monitoring. Potential adverse conditions can occur, namely muscle and body ache which will be self-limited and prevented by this progressive adaptation to exercise. All elderly will have an individual insurance if any adverse event occurs, namely falls during training or any unavoidable accident.

Physical inactivity intervention (V) was previously studied to evaluate potential endocrinological impact [28-30]. This intervention does not aim to promote inactivity but an reduction of the ambulatory usual activity. During these trials the population was physically active and healthy, as it occurs in the studied population, and no long term adverse events were described. As for immediate side effects, only was seen a reduction of insulin sensitivity, cardiovascular fitness evaluated by VO2 and lean leg mass[28]. No adverse events are expected during the duration of the intervention. At the end of the study a series of recommendations and educational advice will be provided also to the participant which will counteract with any potential adverse events of the well known sedentary behavior. Furthermore, a dietary counseling will be provided by a nutritionist which will also be beneficial for the participant.

High fat meal challenge followed by exercise has not previously been studied in this population. An isolated meal is not associated neither with immediate nor long term adverse events. Meal will be made accordingly to the appropriate hygiene rules and after confection will immediately

be provided to the participant. Only in a previous study high fat challenge increase airway inflammation and reduced bronchodilator recovery, but both of the effects were transitory and no side-effects were reported in the tested asthma and obese population[36].

#### Unanticipated Problems

Unanticipated problem is any incident, experience, or outcome that meets all of the following criteria: unexpected (in terms of nature, severity, or frequency) given the research procedures that are described in the protocol-related documents; related or possibly related to participation in the research and related with the research places, subjects or others that puts a greater risk of harm (including physical, psychological, economic, or social harm) than was previously known or recognized. Any incident, experience, or outcome that meets the three criteria above, generally will warrant consideration of substantive changes in order to protect the safety, welfare, or rights of subjects or others. Corrective actions or substantive changes that might need to be considered in response to an unanticipated problem include: changes to the research protocol initiated by the investigator prior to obtaining Ethical Commission approval to eliminate apparent immediate hazards to subjects; modification of inclusion or exclusion criteria to mitigate the newly identified risks; implementation of additional procedures for monitoring subjects; suspension of enrollment of new subjects; suspension of research procedures in currently enrolled subjects; modification of informed consent documents to include a description of newly recognized risks; provision of additional information about newly recognized risks to previously enrolled subjects.

All unanticipated problems will be recorded and reported throughout the study.

